### Strategies to improve adherence to interventions {11c}

To increase compliance, all participants are given a study visit reminder card at the beginning of treatment. This schedule contains an overview of all planned study visits. Additionally, participants are informed that the full study compensation amount of 100 Euro will only be paid at the last study visit (in all other cases, a partial reimbursement will be paid). Furthermore, we aim to increase treatment adherence in the different treatment arms in several ways; in the Buscopan treatment arms, participants are given the first week’s amount of Buscopan pills at treatment visit 1. At this visit, they are instructed to set a reminder on their smartphone to take the pill each day at the same time. Participants are reminded that pills will be counted after each week of treatment. Furthermore, they are requested to note down if they forgot to take a pill. At the weekly visits, the previous week’s pills will be counted in order to check adherence.

In the emotional writing arms, participants are also told to set reminders for all visits on their smartphones. Participants come to the treatment facility to complete each emotional writing session and meet a trained staff member. This encounter is aimed at instilling a sense of accountability toward the staff and the study process. For the natural control group, short weekly phone calls in which mood ratings are given are further aimed at reducing drop-outs in this group.

### Relevant concomitant care permitted or prohibited during the trial {11d}

Concomitant medication is permitted (as long as the medication is not anti-psychotic or of the benzodiazepine substance group) and was kept constant for 4 weeks prior to study entry and the duration of the study. Concomitant psychotherapy is not permitted. Participants who had psychotherapy in the past need to have terminated therapy at least 4 weeks prior to entry in this study.

### Provisions for post-trial care {30}

After participation in the trial, participants are informed about the option to do an intake-interview for post-trial treatment care at our outpatient treatment center or other suitable facilities. All participants receive a monetary compensation (100 Euro) upon completion.

### Outcomes {12}

Since this trial focusses on major depression, the primary outcome will be depression severity assessed at baseline and post-treatment with the expert rating version of the Montgomery Asberg Depression Scale (MADRS) [50]. Subjective depressive symptoms are assessed with the German version of the Beck Depression Inventory (BDI-II) [51] at baseline, post-intervention, and at follow-up, as a secondary outcome. Using these widely used assessment scales is clinically relevant, as expert ratings and subjective assessments of depressive symptoms can vary significantly. By employing both scales, a more comprehensive understanding of changes in symptomatology can be obtained.

Other clinically relevant self-report outcome measures include the German version of the Pain Disability Inventory (PDI) [52] to measure stress and illness burden; the perceived stress scale (PSS-10) [53], both assessed before the allocation, post-treatment, and at follow-up; and the state-subscale of the State-Trait-Anxiety-Depression-Inventory (STADI) [54], which is assessed at baseline, before the allocation, post-treatment, and at follow-up. Changes in treatment expectations prior to the intervention are measured with the following self-report instruments: Treatment Expectation Questionnaire (TEX-Q) [55] and the Generic rating scale for previous treatment experiences, treatment expectations, and treatment effects (GEEE) [56], both assessed at baseline and after the allocation. Side effects and potential harm is measured before the allocation, post-treatment, and at follow-up with the generic assessment of side-effects scale (GASE) [57] (for a detailed description of all variables, see the “Plans for assessment and collection of outcomes {18a}” section).

### Participant timeline {13}

All four intervention arms, as well as the natural course group, have four assessment points (t0, t1, t6, t7; see Fig. 1). At baseline, all participants give informed consent, undergo diagnostic screening, have a medical examination, and fill in the respective baseline measurements (t0). Randomization (into the congruent, incongruent or natural course group) takes place before the second study visit (t1) at which the four intervention groups receive either a biological or a psychological illness explanation. Subsequently, the assignment to the treatment (pharmacological or psychological) is revealed and a treatment rationale according to random assignment is provided. All subsequent study visits are scheduled. This is followed by four consecutive weeks of treatment in the intervention groups (t2-5). The natural course group is also informed about the randomization at t1, and the short weekly phone calls are scheduled. Once the treatment phase is completed, all participants undergo post-intervention diagnostics and fill in the post-treatment measurements (t6). The procedure is completed by a follow-up assessment 1 week after completion of treatments (t7).

### Sample size {14}

We expect a difference of effects on the primary outcome between treatments with congruent versus incongruent contents of a priori provided treatment rationales. Based on previous research [58], we expect an effect size of Cohen’s *d* > 0.40. Our primary hypothesis comprises of the comparison of the clinical status before and after treatment using the MADRS as the primary outcome. A power of 0.90 and alpha < 0.05 and a 2 × 2 design (treatment rationale, active placebo) requires a minimum of 96 participants. Considering a 20% drop-out/treatment discontinuation, 4 groups of 30 participants are required. The 5th group (natural course) does not serve hypothesis testing. Therefore, this group is not considered in the power calculation. Based on the 5 arms in the study, a total of 150 participants are required.

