#### Natural course group

Few clinical studies in the field of antidepressant placebo research include a natural course control group and thus are not able to differentiate between placebo effects and spontaneous remission in the course of the disorder [10]. To control for potential regression to the mean and spontaneous improvement in the outcome variables, we employ a natural course group.

The main aim of this study is to assess how a placebo response in the treatment of depression can be modified by manipulating the patient-clinician communication during the communicated illness and treatment rationale. Thus, the main comparators are the intervention groups who receive congruent vs. incongruent illness and treatment rationales.

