## Statistical methods

### Statistical methods for primary and secondary outcomes {20a}

Multivariate procedures with repeated measures will be used to test the main hypothesis (*F*-statistics). The main analysis of interest is the difference in mean change in the primary outcome (MADRS score) from baseline to post-intervention measurement. In addition, linear mixed-effect models with baseline adjustment will be calculated, based on the generalized covariance matrix. Main effects for group, time, and the group-time interaction will be analyzed. The main analyses are based on intention-to-treat (ITT) models. The predefined covariate variables such as subjective pre-existing attitudes of the participants will be included as covariates. Secondary outcomes of interest, namely subjective depressive symptoms, disability, state anxiety, and perceived stress, will be analyzed with the same strategy as described above.

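### The stated 90% power with 96 participants does not follow from d = 0.40 for the congruent versus incongruent contrast; it would need an unstated pre-post correlation of about 0.8

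*Protocol article*

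**What the plan says.** All from the protocol article.

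- Sample size {14}: the expected difference is "between treatments with congruent versus incongruent contents of a priori provided treatment rationales", and "we expect an effect size of Cohen’s *d* > 0.40". The error rates are given as "A power of 0.90 and alpha < 0.05", and the 2 × 2 "design (treatment rationale, active placebo) requires a minimum of 96 participants". A 20% loss raises this to four groups of 30. The natural course group is left out of the power calculation and brings the total to 150.
- Natural course group: "the main comparators are the intervention groups who receive congruent vs. incongruent illness and treatment rationales". The hypotheses and the trial design section give congruency the same leading place, and allocation is equal across arms.
- Statistical methods {20a}: "Multivariate procedures with repeated measures will be used to test the main hypothesis", using F-statistics. The main quantity is the between-group difference in mean MADRS change from baseline to post-intervention. Baseline-adjusted mixed models are planned in addition.

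The sample size section does not name the test, its degrees of freedom, the SD on which d is standardised, or a correlation between baseline and post-treatment MADRS.

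**The concern.** In a 2 × 2 of rationale by treatment, congruent versus incongruent is the interaction: two arms pooled against two arms pooled, on one degree of freedom. With 96 participants in four equal cells this is 48 against 48. A standardised difference of 0.40 between two groups of 48 is ordinarily detected about half the time, not nine times in ten, so the stated figure looks far too small for the stated effect.

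What is at stake is how the main result will be read. A reader who believes the trial had 90% power will take a non-significant congruency effect as fairly strong evidence against an effect of the planned size. If the power was nearer 50 to 80%, that inference is not warranted.

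**Working it through.** **Inputs.** From the sample size section: d = 0.40 (the lower bound given), power 0.90, alpha 0.05, N = 96 and 20% loss. From the trial design section: equal allocation, hence 48 against 48. Sidedness is not stated; F-statistics imply a two-sided test. The pre-post correlation r is not stated, so it is an assumption and a range is shown.

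**1. Dropout step.** 96 / 0.8 = 120 = 4 × 30. This reproduces.

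**2. Direct reading: d refers to the MADRS change that is analysed.**
- Noncentrality for 48 against 48: 0.40 × √(48 × 48 / 96) = 0.40 × √24 = 1.96. The expected test statistic sits on the two-sided 5% critical value, so power is about one half. The exact noncentral figure is 0.49.
- All 120 evaluable, 60 against 60: 0.40 × √30 = 2.19, power 0.58.
- N for 90% power: per side 2 × (1.960 + 1.282)² / 0.40² ≈ 132, or 264 in total. Noncentral t gives 266; the F-test in four equal cells gives 268.
- A one-sided test does not rescue the figure: power 0.62 at 96, and 216 needed for 90%.

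**3. Alternative reading: d is in raw-score SD.** Baseline adjustment makes the effective size 0.40 / √(1 − r²). A plain change-score analysis makes it 0.40 / √(2(1 − r)).

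| Assumed r | Effective d, baseline-adjusted | Power, 96 completers | Power, 120 evaluable | Power, change score, 96 |
|---|---|---|---|---|
| 0.3 | 0.42 | 0.53 | 0.63 | 0.37 |
| 0.5 | 0.46 | 0.61 | 0.71 | 0.49 |
| 0.6 | 0.50 | 0.68 | 0.78 | 0.58 |
| 0.7 | 0.56 | 0.78 | 0.86 | 0.71 |
| 0.8 | 0.67 | 0.90 | 0.95 | 0.87 |

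With 96 completers, 90% is reached at r of about 0.80 with baseline adjustment and about 0.82 with change scores.

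**4. Where 96 may come from.** Take a repeated-measures group-by-time F-test with four groups, two time points, ρ = 0.5 and f = d/2 = 0.20. The noncentrality is f² × N × 2 / (1 − ρ), with 3 df in the numerator.
- It first reaches 90% power at N = 93. Four equal cells make that 96, where the noncentrality is 0.04 × 96 × 2 / 0.5 = 15.36 and power is 0.91.
- For a contrast of two halves the noncentrality is N × d² / 4. Setting 96 × d² / 4 = 15.36 gives d = 0.80 on the change scale.
- A difference of 0.40 gives 96 × 0.16 / 4 = 3.84, which is f = 0.10 in that test. Power is then 0.33 on 3 df, or 0.49 on the 1 df that congruency uses.

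**5. Effect detectable with 90% power at N = 96.** Unadjusted: d of about 0.67. Baseline-adjusted at r = 0.5: 0.67 × √(1 − 0.25) = 0.58.

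**The case against.** The best defence is that the section leaves room for a reading under which 96 is correct. If d is in raw-score SD, the analysis adjusts for baseline and the correlation is about 0.8, then 96 completers give 90% power at d = 0.40 with nothing doubled. Intention-to-treat analysis of everyone randomised may also retain outcomes from some who discontinue treatment; with all 120 evaluable, power is 0.71 at r = 0.5 and 0.86 at r = 0.7. An article condenses its full protocol, which may record the missing assumptions.

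This stands in part. It rules out a single power figure, and it rules out the inference that 96 can arise only by doubling the effect. Doubling alone does not give 96 for the congruency contrast anyway: at d = 0.80 the 1-df test needs 68, and 96 would give 97% power. The 3-df route is a plausible reconstruction, but the section names no test, so it cannot be stated as fact.

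It does not rescue the published statement. The point is a stated number that its stated inputs do not produce, rather than a missing detail, and the correlation that would produce it appears nowhere in the article.

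A reader might also infer from "Our primary hypothesis comprises of the comparison of the clinical status before and after treatment using the MADRS as the primary outcome" that the primary hypothesis has become a within-group comparison. The text does not support this. The section opens with the between-arm difference, and the sentence can be read as describing MADRS change as the outcome, in line with the primary outcome and statistical methods sections.

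**Conclusion.** The sample size statement is wrong as written. For the 1-df congruency contrast at d = 0.40, two-sided alpha 0.05:

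- d on the analysed change: power about 0.49 with 96 completers and 0.58 with all 120; about 266 participants would be needed for 90%.
- d in raw-score SD with baseline adjustment: about 0.53 to 0.78 with 96 completers for r from 0.3 to 0.7; 90% only at r of about 0.8.

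These figures assume equal cells and, for the second line, a correlation that the protocol does not give. Gains from covariates other than baseline MADRS are not counted. A flat 49% is therefore one scenario and not the trial's established power. The firm conclusion is that 90% is not supported by what the section states, and that a null congruency result should not be interpreted as if it were.

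**What to change.** Keep N = 150. In the sample size section:

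1. State the test, its degrees of freedom, the SD on which d is standardised and the assumed baseline-to-post correlation.
2. Replace the 90% claim with the power delivered for the 1-df congruency contrast. For example: with 96 completers (48 congruent, 48 incongruent), two-sided alpha 0.05 and d = 0.40, power is about 0.49 unadjusted and about 0.5 to 0.8 with baseline adjustment for r between 0.3 and 0.7.
3. Add the effect detectable with 90% power: d of about 0.67 unadjusted, or about 0.58 baseline-adjusted if r = 0.5. If the full protocol records another correlation, use that one and say so.

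In the reporting plan, commit to giving the congruency contrast with its 95% CI and to not reading non-significance as absence of effect.

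Cost: text only and no added participants. The price is that a stated figure becomes less favourable.

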### Recruitment {15}

Participants will be recruited using flyers in public spaces and healthcare practices, posts in depression self-help forums, social media advertising, and through email lists of the university staff and students. In addition, patients with a primary diagnosis of depression, who are on the waitlist of the university's outpatient clinic, will be approached.

## Assignment of interventions: allocation

### Sequence generation {16a}

Each participant is allocated a number in ascending order from 0 to 149. Participants will be randomized using the Python Package randomization [59] by setting a seed and randomly assigning the 150 subjects to the five treatment arms. A reproducible script is available and will be published after completion of data collection.

### Concealment mechanism {16b}

The allocation (treatment vs. natural course group) as well as the specific allocation within the treatment groups (biological vs. psychological illness rationale; pharmacological vs. psychological placebo treatment) will remain concealed via opaque, sealed envelopes until the start of the treatment phase.

### Implementation {16c}

One investigator, who has no contact with the participants, runs the custom-made script which randomly allocates numbers 0–149 (*N* = 150) to the five conditions. These allocations, including the allocation to the active or control group, the allocation to the treatment rationale (biological or psychological), and the allocation to the treatment condition (pharmacological or psychological placebo), are kept in separate sets of sealed, opaque envelopes. All envelopes are prepared and sealed prior to the start of the study by the investigator.

Once a participant is included in the study, they receive a randomization number (0–149 in ascending order) from the staff member who completed the diagnostic interview. None of the staff, who administer the treatments or assessments, have access to the complete allocation list. The clinician who administers the illness rationale opens the envelope containing the information about whether the participant is allocated to the psychological or biological illness rationale or to the natural course group, before meeting the participant for the second appointment. The envelope indicating the treatment allocation is opened in front of the participant after the illness rationale was given. This ensures that the illness rationale is provided without knowledge of whether the participant receives a congruent or incongruent treatment afterwards.

## Assignment of interventions: blinding

### Who will be blinded {17a}

Participants will be blinded to the congruency condition. Blinding (to group allocation and congruency condition) of the outcome assessors (during baseline and post-assessments) is achieved by having separate clinicians administer the outcome assessments and the illness and treatment rationales. Clinicians who provide the illness rationale will be blinded to the participants’ treatment allocation up to the point at which the respective treatment allocation is revealed. The research staff members who administer the treatment afterwards are blinded to the congruency condition as well.

### Procedure for unblinding if needed {17b}

Unblinding is permissible if a participant becomes a drop-out or shows a marked increase in depressive symptoms and/or suicidal tendencies and is removed from the study. All participants will be debriefed orally and in writing about the aims of the study and group allocation after the study is completed. All participants are also debriefed about the congruency condition and receive both illness rationales upon study completion.

## Data collection and management

### Plans for assessment and collection of outcomes {18a}

#### Primary outcome

The primary outcome is the change in depression severity as measured by the expert rating version of the Montgomery Asberg Depression Scale (MADRS) [50]. The MADRS assesses the following: apparent sadness, reported sadness, inner tension, reduced sleep, reduced appetite, concentration difficulties, lassitude, inability to feel, pessimistic thoughts, and suicidal thoughts. Each item is scored on a scale from 0 (no/hardly any difficulties) to 6 (extreme difficulties). Total scores between 7 and 19 indicate a mild depression, scores between 20 and 34 moderate depression, and a score above 34 severe depression [60]. This scale was shown to achieve high reliability of total and item scores in depressed populations [61]. Blinded and trained clinicians undertake the MADRS assessment at baseline and post-intervention. The outcome assessors are trained to rate the MADRS scores alongside the depression section in the Structured Interview for DSM-5 (SCID-5) diagnoses. A random selection of videotaped MADRS ratings will be rated a second time by independent raters to establish inter-rater reliability.

#### Secondary outcomes

A change from baseline in subjective depressive symptoms is measured using the aggregate score on the German version of the Beck Depression Inventory (BDI-II) [51]. It shows high reliability, with Cronbach’s alphas ranging from 0.84 to 0.90 in German clinical and non-clinical samples [62]. Additionally, the following secondary outcomes will be assessed:A change from baseline in subjective disability is measured using the aggregate score of a modified version of the German Pain Disability Inventory (PDI) [52]. This version of the PDI was shown to have high internal consistency (Cronbach’s alpha of 0.93) [52].The state-subscale score of the State-Trait-Anxiety-Depression-Inventory (STADI) will be used to assess a change from baseline in anxious-depressive symptoms [54]. The STADI also has high reliability in all subscales [63].The aggregate score on the perceived stress scale (PSS-10) is used to assess changes from baseline in subjective stress experience [53]. Cronbach’s *α* was 0.84 in a German sample, indicating good reliability [64].The generic assessment of side-effects scale (GASE) will be used to assess experience and attribution of side effects with respect to both treatment types [57]. The GASE was shown to have high internal consistency with Cronbach’s *α* of 0.89.Treatment expectations are assessed using the Treatment Expectation Questionnaire (TEX-Q) [55], which shows good internal consistency for all subscales and the sum score (Cronbach’s *α* = 0.71–0.92) [65] and the generic rating scale for previous treatment experiences, treatment expectations, and treatment effects (GEEE) [56]. Psychometric properties of this scale are currently under evaluation.

#### Pre-defined covariates

There are several trait variables, which were shown to influence placebo responses. Some of these variables will be measured and assessed as covariates. They are assessed only at baseline.The trait-subscale of the State-Trait-Anxiety-Depression-Inventory (STADI) will be used to control for anxious-depressive symptoms as a stable personality trait [54].A German version [66] of the Somatosensory Amplification Scale (SSAS) [67] will be assessed to control for tendencies to experience and amplify somatic and visceral sensations. The original scale showed adequate internal consistency (Cronbach’s *α* = 0.82) [67].We will also control for the sensitivity to pleasant incentives using the behavioral inhibition/approach system sensitivity scale (BIS/BAS) [68]. Internal consistency was adequate for the German version [69] with a Cronbach’s *α* of 0.76 (BIS) and 0.79 (BAS) in a German population sample [70].Finally, pre-existing experience with psychotherapy and antidepressants, measured with the “prior experience” subscale of the GEEE [56].Objective stress will be assessed in two ways: (1) salivary cortisol awakening response and (2) salivary alpha-amylase (sAA) activity, as markers for HPA-axis and sympathetic activity. The cortisol samples will be taken on two consecutive mornings (immediately after waking, 30 and 45 min after awakening) following the baseline assessment.

All other data is collected by the trained research staff. The research staff is blinded at baseline (no allocation has taken place yet). At all other assessment points, the research staff is blinded to the congruency condition. Since all secondary outcomes are self-reported, participants are instructed to fill in the questionnaires in the digital platform (Lime Survey), which makes data transfer from paper–pencil questionnaires into the digital platform obsolete. As part of the diagnostic process at baseline, the BDI-II is also assessed in paper–pencil format, which will later be used to check for consistency between the paper–pencil and digital entries at baseline.

